### Sample size calculation

The sample size was calculated based on a similarly designed RCT (45). Assuming a statistical power of 90% with a clinically significant minimum effect of 0.5 (Cohen's d) and alpha 5%, a total of 88 subjects will be needed (44 in the EG and 44 in the CG). Given this is a long-duration study, a drop-out rate of 10–20% was estimated.

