### Statistical analysis

All analyzes will be performed using the Statistical Package for the Social Sciences-SPSS® (82). Specific and sociodemographic variables will be expressed generally and between intervention groups in relative and absolute frequencies, means, medians, standard deviation, and 95% confidence interval. Continuous variables will be evaluated by the *T*-student or U-Mann Whitney-test according to their distribution and the qualitative ones by the *X*^2^-test. The distribution of variables will be evaluated using the Shapiro Wilk. The global significance level adopted is 0.05. To determine the effects of intervention throughout the study (main outcome and other scales), repeated measures ANOVA (two-way) will be applied, considering the temporal effect of visits (v-0 to v-final) and the intervention effect (EG × CG). In identifying the significant interaction effect, one-way repeated measures ANOVA test or its non-parametric alternative (Friedmann test) will be performed to verify that the effect is independent of treatment. Contingency tables and *X*^2^-tests will be applied to compare responders and non-responders in the intervention groups. Analysis using intent-to-treat (ITT) will be employed to assess the results (83). Vital signs will be assessed using two repeated measures ANOVA (two-way). First, considering the effect of the intervention immediately (3 evaluations at each visit) and the second, evaluating the effect of the intervention on VS over time (acute and maintenance treatment).

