### Reasons for withdrawal or termination

Subjects who meet one or more of the criteria outlined below will be withdrawn from the study:

Intolerance to medications;Abnormal results on lab tests;Serious adverse event;The above-mentioned items will be assessed individually by the team according to medical criteria. Prolonged arterial hypertension, serious allergies, abnormal heart rate, or worsening of pre-existing diseases, among others, will be checked. Manic switching, imminent risk of suicide, attempted suicide, severe psychotic symptoms, aggressiveness, etc. will constitute grounds for study withdrawal.Relapse or lack of response in Phases II or III. Lack of response will be defined as reduction or maintenance of scores on the index scale of ≤25%, whereas relapse will be the attainment of scores <50% in individuals who had achieved remission or response during the study.Two consecutive visits missed;Withdrawal of consent for the study.

Patients who discontinue the study shall be given guidance to continue outpatient psychiatric treatment.

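### Patients who respond poorly or relapse leave the study, not only the treatment, so later outcome data are lost selectively and the ITT maintenance comparison is compromised

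*Protocol article*

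**What the plan says.** All references are to the protocol article.

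- **Reasons for withdrawal or termination.** The list opens with "Subjects who meet one or more of the criteria outlined below will be withdrawn from the study". One listed reason is "Relapse or lack of response in Phases II or III. Lack of response will be defined as reduction or maintenance of scores", completed by a 25% limit on an index scale that is not identified. The same sentence adds that "relapse will be the attainment of scores <50% in individuals who had achieved remission or response during the study". The only step described afterwards is advice to continue care as an outpatient.
- **Measures and outcome variables.** MADRS is the primary outcome measure. It is rated three times a week in PII, then weekly in PIII and in the post-treatment phase (PIV).
- **Statistical analysis.** The main outcome is analysed by two-way repeated-measures ANOVA from the first to the final visit, and "Analysis using intent-to-treat (ITT) will be employed to assess the results".
- **Cognitive assessments.** The second round of neuropsychological tests falls at the end of PIII.
- **Study hypotheses.** The principal hypothesis is that the two treatments have similar efficacy.
- **Sample size calculation.** "a drop-out rate of 10–20% was estimated", with no statement of what counts as drop-out.

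**The concern.** A rule based on outcome scores ends observation, not only treatment. From then on the trial holds no data on the patients who did worst, and the arm with the poorer results loses more of them. The analysis is meant to cover all randomised patients through the last visit, but the withdrawal rule ensures that many of those values are never collected. An analysis plan can choose how to handle missing ratings; it cannot recover ratings that were not taken.

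What is at stake is the maintenance comparison, which is the trial's main novelty, and the long-term cognitive comparison. Because the hypothesis is similarity and the article states no margin, a method that makes two arms of survivors look alike would favour the hoped-for conclusion.

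**Working it through.** **1. The plan's own figures.** The 10–20% drop-out estimate has no derivation to reproduce. The sample size of 88 is a separate matter and this point does not depend on it. Only its effect size, "clinically significant minimum effect of 0.5 (Cohen's d", is borrowed below.

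**2. How often could the non-response limit be met?** The Introduction reports MADRS changes (mean, SD) to day 15 in the repeated-infusion RCT on which the sample size is based. Baseline MADRS is not given; 28 to 38 is assumed. With baseline B, mean reduction m and standard deviation SD, a normal model gives

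P(reduction ≤ 25%) = Φ((0.25·B − m)/SD).

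| Arm in that RCT | m, SD | B = 28 | B = 38 |
|---|---|---|---|
| Ketamine twice weekly | 18.4, 12.0 | Φ(−0.95) = 17% | Φ(−0.74) = 23% |
| Ketamine three times weekly | 17.7, 7.3 | Φ(−1.47) = 7% | Φ(−1.12) = 13% |
| Placebo, twice weekly | 5.7, 10.2 | Φ(0.13) = 55% | Φ(0.37) = 64% |
| Placebo, three times weekly | 3.1, 5.7 | Φ(0.68) = 75% | Φ(1.12) = 87% |

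The control here is active, so the placebo rows do not predict its rate.

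**3. Effect on a completer comparison.** Assumed: baseline 32 (limit 0.25 × 32 = 8 points), SD of change 11, true difference 5.5 points (5.5/11 = 0.5 SD), correlation ρ between end-of-PII and end-of-PIII change of 0.5 to 0.9, and one check at the end of PII. With a = (8 − m)/11 and λ(a) = φ(a)/(1 − Φ(a)), the mean later reduction among those kept is m + ρ·11·λ(a). The completer difference is therefore

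5.5 − ρ·11·(λ_worse − λ_better).

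- Mean reductions 18 and 12.5: a = −0.909 and −0.409; withdrawn 18% and 34%; λ = 0.322 and 0.557. Difference: 4.2 (ρ = 0.5) to 3.2 (ρ = 0.9).
- Mean reductions 17 and 11.5: a = −0.818 and −0.318; withdrawn 21% and 38%; λ = 0.360 and 0.607. Difference: 4.1 (ρ = 0.5) to 3.1 (ρ = 0.9).

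Monte Carlo runs with the same baseline, SD, difference and correlations, differing in details that the documents do not fix, widen this to about 17–29% versus 33–48% withdrawn and a completer difference of about 2.7–4.3 points.

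**4. Other assumptions.** With baseline about 33, ρ = 0.8, one check and a true difference of 0.5 SD:

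| SD ketamine / control | True difference | Completers | Kept |
|---|---|---|---|
| 12 / 12 | 6.0 | 3.6 | 60% |
| 12.0 / 10.2, ketamine better | 5.6 | 4.5 | 81% |
| 12.0 / 10.2, control better | 5.5 | 2.4 | 43% |
| 7.3 / 7.3 | 3.6 | 2.7 | 73% |
| 7.3 / 5.7, ketamine better | 3.3 | 3.2 | 98% |
| 7.3 / 5.7, control better | 3.3 | 1.8 | 54% |

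With equal means and equal SDs there is no bias. With equal means but SDs of 12.0/10.2 or 7.3/5.7, completers show a spurious difference of about 1.1 or 0.8 points in favour of ketamine.

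**5. Against the drop-out estimate.** With 44 per arm, step 3 gives 8 + 15 = 23 to 9 + 17 = 26 of 88 patients, that is 26–30%, from the non-response limit alone.

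**6. Does the analysis method matter?** Yes. In the step 3 setting with mean reductions 18 and 12.5, a likelihood-type estimate that uses the observed end-of-PII score returns 5.5. Carrying the last value forward gives about 5.6 to 6.1.

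**The case against.** Several points on the other side stand.

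- The score that triggers withdrawal is observed. A reader might infer that the primary outcome goes missing because of its own value; the documents do not support that. Later values are missing because of earlier recorded ones, which a likelihood-based model can largely handle. The bias comes from combining the withdrawal rule with a completer analysis. The article names ANOVA and ITT but no missing-data method, and an unseen analysis plan may supply one. It is therefore too strong to say that ITT is defeated outright.
- Bias toward similarity is not guaranteed. It needs a true difference and a completer analysis; step 4 shows almost no shrinkage in one case and a spurious difference in another.
- The conflict with 10–20% is not textual. The article does not say whether drop-out includes withdrawals required by the rules, and the excess appears only under assumed inputs.
- The index scale need not be MADRS. HAM-D is the eligibility scale and follows the same schedule from PII to PIV.
- Read literally, the relapse clause describes a low score, and a reader might infer that responders would be removed for improving. It follows a clause stated as percentage reduction, so improvement falling below 50% is the natural reading. The wording needs clarifying; it does not show that responders would be removed. Likewise, the missing assessment time does not show that patients would be removed within days, and a full protocol may give it.
- If the rule is applied only at the end of PII, the acute comparison is untouched.
- Chi-square tests of responders against non-responders by arm are already planned.

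What these points leave intact is that the article states withdrawal from the study and describes no ratings afterwards. No model replaces data never collected, least of all cognitive tests given only before treatment and at the end of PIII.

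**Conclusion.** The concern holds in a limited form. The withdrawal rule and the stated ITT analysis from first to final visit do not fit together: outcome data in maintenance, and cognitive data at its end, are lost selectively according to earlier observed scores. Under the planned ANOVA, in its conventional complete-visit form, the maintenance comparison is between groups selected on outcome after randomisation.

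The size can only be illustrated. One set of assumptions leaves about 2.7–4.3 of 5.5 true points; others leave 43–98% of the truth. These figures rest on an assumed baseline, correlation, arm means and a single check, none of which the documents give. Rule-driven withdrawal alone could exceed the drop-out estimate under such inputs, but that is a possibility, not a demonstrated contradiction. The loss of data follows from the text and is firm; the direction and size of bias are conditional.

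**What to change.** 1. Separate stopping study medication from leaving the study. Unless consent is withdrawn, patients who stop for lack of response or relapse keep their scheduled MADRS ratings and the end-of-PIII cognitive tests.
2. Analyse all patients as randomised with a likelihood-based mixed model that uses every observed visit, in place of complete-case ANOVA.
3. Report non-response and relapse by arm as outcomes, extending the responder comparison already planned.
4. Ask the sponsor to reconcile the relapse wording, the unnamed index scale, the time at which lack of response is judged, and the drop-out estimate. No threshold, scale or clinical rule is proposed here.

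The cost is a protocol amendment and some extra ratings on the existing schedule. Ratings after medication stops will include the effect of other care and must be described as such. The article says the study is already running, so each further withdrawal without follow-up is a permanent loss.

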### Measures and outcome variables

The study will assess (given in Table 1):

Sociodemographic variables: gender, marital status, ethnicity, number of children, income, education, and employment.Clinical characteristics over the life course: clinical and psychiatric comorbidities, smoking, family history of mood disorders, prior pharmacological treatment and ECT, number of mood episodes, previous psychiatric admissions, suicide attempts, currently receiving psychotherapy, and history of sexual, or physical abuse.Clinical history: visits to the emergency room, attempted suicides, or psychiatric hospitalizations.The Montgomery-Åsberg Depression Rating Scale (MADRS) (70, 71): will be applied as a primary outcome measure 3× per week for the first month (PII), 1× per week for 6 months (PIII), and 1× per week (PIV) for 1 month.The Hamilton Rating Scale for Depression (HAM-D) (72, 73): will be applied once in PI to assess symptom severity and again 3× per week for 1 month (PII), 1× per week for 6 months (PIII), and 1× per week (PIV) for 1 month.Vital signs (VS): pulse oximetry, heart monitoring, breathing rate, heart rate, and blood pressure will be checked continuously using non-invasive methods. VS to be monitored 3× per week for the 1st month (PII) and 1× week (PIII) for 2 h continuously after completion of each application.Global Clinical Impression (GCI) scale: this will be applied 3× a week for 1 month (PII), 1× week for 6 months (PIII), and 1× week (PIV) to assess disease severity, global improvement of the condition and hence, treatment efficacy (74).Depression Thoughts Scale (DTS): the DTS will be applied at visit one (V-1), V11, and V-39 to assess for thought distortions (75, 76).Clinician-Administered Dissociative States Scale (CADSS): this will provide a measure of the dissociative effects of ketamine and will be applied 3× per week for the 1st month (PII), and 1× per week for 6 months (PIII), ~1 h after application of injections (77).Young's Mania Rating Scale (YMRS): this scale will be employed in this study to assess manic switching as an adverse effect of the medications and applied 3× week for the 1st month (PII) and 1× week for 6 months (PIII), ~1 h after application of injections (78).Brief Psychiatric Rating Scale (BPRS): Sub-item 12 of the scale will be used for detecting the presence of psychotic symptoms arising after application of ketamine, applied 3× week for 1 month (PII) and 1× week (PIII), ~1 h after application of injections (79).Udvalg Kliniske Undersoegelser Side Effect Rating Scale (UKU-SERS): this will be used to determine the presence of side effects of the medications used and will be applied 3× week for the 1st month (PII) and 1× week (PIII) thereafter, around 1 h after application of injections (79).World Health Organization Quality of Life, brief version (WHOQOL-Bref): this scale will be applied at V-1, V-11, and V-35 (80).Sheehan Disability Scale (SDS): this scale will be applied at V-1, V-11, and V-35 (81).

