### Intervention

Two groups will be formed: a study group and an active control group. The study group will receive dextroketamine chloralhydrate IM (0.75 mg/kg) plus 2 placebo tablets orally, one in the morning and the other at night. The active control group will receive saline solution IM plus one of the alternative therapies for TRD: escitalopram 15 mg (morning) or aripiprazole 5 mg (night) (10). Injections will be applied alternately to gluteal muscles in the external upper quadrants. For 4 weeks (1 month), applications will be applied on Mondays, Wednesdays, and Fridays (giving a total of 12 interventions). For the ensuing 6 months, applications will be weekly (giving a total of 24 interventions). For 4 weeks (1 month), participants will continue to receive the tablets (active treatment or placebo) and be monitored. Safety parameters: vital signs will be monitored continuously by the researchers for 2 h post-application: fingertip pulse oximetry, heart rate, breathing rate, blood pressure, and electrocardiography. Abnormal blood pressure will be defined as low <90/60 mmHg and high >140/90 mmHg. Abnormal heart rate will be defined as <60 or >100 bpm. Abnormal breathing rate will be defined as <10 cycles/min or >20 cycles/min. Low oxygen saturation will be defined as levels <95%. Collateral symptoms such as nausea and vomiting will be managed using ondansetron 8 mg sublingually (SL). Individuals presenting episodes of anxiety, hallucinations, or intense dissociative effects will be given clonazepam SL 0.25 mg. An emergency team will be deployed in the event of serious acute events such as heart arrhythmia or prolonged hypertension. Patients will be placed under observation in a quiet comfortable environment and will be cleared to leave after 2 h, accompanied by a competent adult.

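### Two consecutive missed visits remove a patient from the study, not only from treatment, so MADRS ratings that a returning patient could still give are avoidably lost

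*Protocol article*

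**What the plan says.** Reasons for withdrawal or termination opens with the consequence that governs its whole list: "Subjects who meet one or more of the criteria outlined below will be withdrawn from the study". One listed criterion is "Two consecutive visits missed". The sentence that provides for individual medical assessment refers back to the items before it (intolerance, laboratory results, serious adverse events), so it does not reach the missed-visit item. That item names no phase, whereas the relapse and non-response item is limited to Phases II and III. Withdrawal of consent is a separate item. The only provision for what follows is "Patients who discontinue the study shall be given guidance to continue outpatient psychiatric treatment".

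Measures and outcome variables says that the MADRS "will be applied as a primary outcome measure 3× per week for the first month (PII), 1× per week for 6 months (PIII"), and then weekly for one month in the post-treatment phase (PIV). Intervention gives the spacing in the acute phase (PII): "applications will be applied on Mondays, Wednesdays, and Fridays (giving a total of 12 interventions"). For maintenance (PIII) it says: "For the ensuing 6 months, applications will be weekly (giving a total of 24 interventions").

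Statistical analysis states "Analysis using intent-to-treat (ITT) will be employed to assess the results" and, for the main outcome, "repeated measures ANOVA (two-way) will be applied, considering the temporal effect of visits (v-0 to v-final").

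**The concern.** An intention-to-treat comparison is best served by measuring every randomised patient for as long as the patient agrees, whether or not study treatment continues. This rule joins two decisions that can be taken separately: stopping treatment after a gap in attendance, and ending observation. The first is a clinical matter and is not questioned here. The second costs data on the primary outcome.

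The loss is avoidable only in one group. The two missed ratings are gone under any rule, and a patient who never returns loses nothing more because of it. A patient who returns and still consents could be rated at the remaining scheduled visits. Without those ratings, the intention-to-treat result depends more on assumptions about unseen scores.

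**Working it through.** **Inputs from the article.** MADRS visits: 12 in PII (three per week for 4 weeks), 24 in PIII (weekly for 24 weeks) and 4 in PIV (weekly for 4 weeks). Total: 12 + 24 + 4 = 40. Randomised patients: 88, so 88 × 40 = 3,520 scheduled ratings. The article gives no miss rate and no return rate, and no figure of its own on this point to reproduce.

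**When the rule triggers.**
- PII, Monday/Wednesday/Friday: last attended Monday, second miss Friday, 4 days. Last attended Wednesday, second miss Monday, 5 days. Last attended Friday, second miss Wednesday, 5 days.
- PIII, weekly: second miss 14 days after the last attended visit.
- A patient who returns at the very next visit has been away 7 days in PII or 21 days in PIII.

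**What one patient can lose.** If the second miss is visit k of 40, then 40 − k ratings remain.
- Attends visit 1, misses visits 2 and 3: 40 − 3 = 37 (9 in PII + 24 in PIII + 4 in PIV).
- Second miss at the last PII visit (k = 12): 28.
- Second miss within PIII (k = 13 to 36): 27 down to 4.
- Second miss within PIV (k = 37 to 40): 3 down to 0.

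These are maxima. They assume that the patient returns, attends everything afterwards and is not withdrawn for another reason.

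**How often it might happen (illustration only).** Assume misses are independent, with constant probability p per visit, and nobody is removed for other reasons. Let a be the probability of not having triggered with the last visit attended, and b the same with the last visit missed. Start at a = 1, b = 0. At each visit a becomes (a + b)(1 − p) and b becomes a·p, using the old values. After n visits, P(triggered) = 1 − a − b.

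| p | 36 injection visits | of 88 | all 40 visits | of 88 |
|---|---|---|---|---|
| 2% | 1.4% | 1 | 1.5% | 1 |
| 5% | 8.0% | 7 | 8.9% | 8 |
| 10% | 27.6% | 24 | 30.2% | 27 |

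**Ratings forgone over 40 visits.** Let f(k) be the probability that the rule triggers at visit k. If every such patient returns and attends at rate 1 − p, the loss is 88 × Σ f(k)(40 − k)(1 − p).

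| p | all return | half return |
|---|---|---|
| 2% | 25 (0.7% of 3,520) | 12 (0.4%) |
| 5% | 144 (4.1%) | 72 (2.0%) |
| 10% | 484 (13.7%) | 242 (6.9%) |

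**Link to the analysis method.** A classical repeated measures ANOVA uses only patients with every visit present. Under the same assumption the chance of at least one miss in 40 visits is 1 − (1 − p)^40: 55%, 87% and 99% at p = 2%, 5% and 10%. Patients who trigger the withdrawal rule are already among those excluded, so keeping their later ratings helps the primary comparison only if the method can use partial data.

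**The case against.** The strongest objection is that the loss is inferred. The article never says that ratings stop, and a condensed article may leave the follow-up of withdrawn patients to the full protocol. That limits the wording to what follows if the text is applied as written. It does not dispose of the point, because leaving the study is a stated conduct rule, and no later analysis plan can recover ratings that were not taken.

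Second, under a classical ANOVA the patient is dropped at the first miss, so the rule costs the primary comparison nothing further. This stands. The benefit depends on changing the analysis as well.

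Third, the frequencies rest on assumed rates, and the other withdrawal criteria would leave fewer patients exposed. This also stands: at 2–5% missed visits with half returning, the loss is 0.4–2.0% of ratings. The 10–20% drop-out in Sample size calculation does not settle the matter, since it is not a rate of missed visits.

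Fourth, the relapse and non-response criterion in the same list depends on the outcome itself and is the more serious case of the same design fault. That is fair, but it does not make this item sound.

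A reader might go further and infer that the rule contradicts the intention-to-treat analysis or biases the comparison in a known direction. The article supports neither. Withdrawn patients can remain in the analysis set with the data they gave, and nothing in the text shows that missed visits would differ between arms.

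**Conclusion.** The point holds in a limited form. The rule as written ends study participation after a short absence, makes no provision for return or for further ratings, and so forgoes obtainable primary-outcome data from consenting patients who come back. The size for one such patient is firm: up to 37 of 40 ratings after at least one attended visit, and at most 3 once the patient is in PIV. The size for the trial is unknown. The illustrative 1–8% of patients over the 36 injection visits assumes independent misses at 2–5% and no other removals; the larger losses need a 10% miss rate and every affected patient returning. It is a weakness in data retention, worth correcting because the correction is cheap.

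**What to change.** 1. Make two consecutive missed visits at most a reason to stop study treatment, not to leave the study. Apply this identically in both arms without revealing allocation; an instruction for one arm only could unblind.
2. Allow usual care after study treatment stops, which needs an exemption from the ban on other psychiatric medication in Inclusion and exclusion criteria. Continuing on tablets alone would leave ketamine-arm patients on placebo.
3. Have blinded raters continue the MADRS at the remaining scheduled visits that the patient attends, including those in PIV, unless consent is withdrawn.
4. Include those ratings in the intention-to-treat analysis with a method that uses incomplete cases, such as a mixed model for repeated measures. Without this step the first three add little to the primary result.

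The cost is a short amendment covering follow-up status, usual care and the analysis method. No visits or patients are added. Some later ratings will reflect usual care rather than the assigned treatment, which is what an intention-to-treat comparison accepts.
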